### Recruitment

Participants are recruited via advertisements campaigns on (social) media, posters, and flyers in public spaces and patient organizations. After inclusion of a rMDD participant, a ND control participant is matched based on their age, sex, and education level.

### COVID-19 related changes to the study design

At the time of data collection (March 2020), the COVID-19 pandemic started which led to a delay in the data collection. We therefore had to change the original protocol in order to collect data of a sufficiently large sample within the funding period. We decided to split the study into two phases: phase 1) including the original measurements as written in this protocol paper but with 25 rMDD and 25 ND control participants and phase 2) including the questionnaires, cognitive task and ESM measurements as described in this protocol paper but without the physiological measurements in the form of an online study with *n* = 25 participants per group. This way, we will have a sample of *n* = 25 participants per group for the EEG, ECG/ICG, and actigraphy data and a sample of *n* = 50 participants per group for the ESM, questionnaires, and cognitive task data. Data collection to reach the desired sample size for these two phases is still ongoing and expected to finish in June 2024.

The power analyses of the original study were calculated based on questionnaire data. The sample size for the questionnaire, cognitive task and ESM data will therefore not change. For the physiological measurements (laboratory EEG, ambulatory ECG/ICG, and actigraphy; part 1) we performed a new power analysis. Our power analysis is based on a study of Jin et al. [37], which has a similar EEG task setup as in the current study. They examined differences between event-related potentials related to on-task behaviour versus mind-wandering behaviour which is similar to our intended analysis of comparing ruminative vs. non-ruminative trials [51]. They found a difference in the P3 component between being on-task and when mind-wandering [*t* = 3.97, *p* < 0.001, *d* = 0.59]. Using G*Power 3.1.9.7, a target sample size based on this result was calculated. To conduct a one sample t-test with a statistical power of 80%, a sample size of *n* = 20 participants is needed to draw reliable conclusions about treatment effects on PC measured with EEG.

For the physiology, we rely on a study of Ottaviani et al. [52] in which the differences between HR in individuals with MDD and healthy controls were examined. They found a significant difference in HR between MDD- and healthy control-participants with an effect size of *d* = 0.96. This effect size was used to calculate the sample size using G*Power 3.1.9.7. To conduct two-tailed t-tests with a statistical power of 80%, a sample size of 19 participants per group is sufficient to draw reliable conclusions.

Together, this suggests that a sample size of *n* = 25 participants per group for (neuro)physiological measurements is sufficient to examine the effects of interventions and differences between the rMDD and ND groups.

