#### Exclusion criteria

Furthermore, individuals who meet any of the following criteria are excluded from participation in this study:Fulfilling criteria for any current DSM-5 diagnosis as objectified with the Structured Clinical Interview for DSM-5 (SCID-5) [48];Daily use of anti-depressive medication, benzodiazepines, methylphenidate, beta blockers or other medication potentially influencing ICG/ECG currently or in the last four weeks;Recent engagement (defined as in their last episode, or as one year prior to inclusion in case the last episode was more than a year before inclusion) in PCT including the positive fantasizing technique and/or have recent experiences (defined as daily practice in the past two years for at least two weeks) with mindfulness, meditation, or mindful yoga. This criterion prevents underestimation of true effects of the interventions and maximizes treatment effects;Participation in another clinical intervention study at the moment of inclusion in the study to prevent overlapping intervention effects.

Individuals for the ND control group who additionally meet any of the following criteria are excluded from participation in this study:Presence of symptoms of depression according to the IDS-SR30 (score > 13), to make sure they are not currently experiencing clinically relevant depressive symptoms;Any life-time psychopathology of any disorder as objectified with the SCID-5.

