### Sample size

To our knowledge, we are the first to combine ESM, ICG/ECG measures, and laboratory EEG measures to study the effects of different interventions on PC. It is difficult to do power calculations for our study since there is no software available that can make predictions for our chosen statistical methods (linear mixed effect models & generalized additive models; see Statistical Analyses). We therefore calculated the sample sizes using G*Power (version 3.1.9.4) for t-tests based on questionnaire measures.

In order to study the differential effects between mindfulness and positive fantasizing on PC in individuals vulnerable for depressive relapse, we will include 50 rMDD participants. In a meta-analytic review, Perestelo-Perez et al. [49] compared the effects of Mindfulness-Based Cognitive Therapy with usual care on rumination in patients with a current depressive disorder or a depressive disorder in the past. They observed a Hedges’ *g* of -0.59 for the effect of Mindfulness-Based Cognitive Therapy compared to usual care in reducing ruminative thinking. Using G*Power 3.1.9.4, sample sizes based on these outcomes were calculated. We expect PC to reduce after mindfulness and positive fantasizing. Therefore the sample size for one-tailed t-tests was calculated. To conduct one-tailed t-tests with a statistical power of 80%, the sample size should be *n* = 36 participants. A sample size of *n* = 50 rMDD participants should therefore give sufficient power to draw reliable conclusions about treatment effects, especially since questionnaires are a less sensitive measure than most of the other measurements used in the current study (i.e., ESM, ICG/ECG and laboratory EEG). This relatively large sample size also helps us to buffer against inevitable data losses related to e.g., participants not completing all questionnaires or technical malfunctions of the physiological measurements.

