To conduct reliable between-group comparisons on how the effects of mindfulness and fantasizing on PC differ between rMDD and ND individuals, we will include 50 ND participants that are matched to the 50 rMDD participants on age, sex, and education level. In a study of Lois and Wessa [50], they compared self-reported rumination scores between rMDD individuals and matched healthy controls at a baseline level. They observed a t-value of *t*(48) = 2.4 (effect size Cohen’s *d* = 0.686) comparing rumination scores between rMDD participants and controls. Based on these outcomes, sample sizes were calculated using G*Power 3.1.9.4. No specific direction of effects was hypothesized for the effects of mindfulness and fantasizing on PC in rMDD versus ND individuals. Therefore, the sample size for two-tailed t-tests was calculated. To conduct two-tailed t-tests with a statistical power of 80%, sample sizes should be *n* = 28 participants per group. This suggests a sample size of *n* = 50 participants per group should give sufficient power to draw reliable conclusions about between-group differences in changes in PC.

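### The statements that 25 and 50 participants per group suffice for intervention effects and group differences in change are not supported, because each calculation uses the effect size of another contrast

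*Protocol article*

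**What the plan says.** The Sample size section explains that no software covers the planned mixed and additive models, so t-tests on questionnaire measures stand in for them.

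- **Mindfulness versus fantasizing in rMDD.** The input is g = -0.59 from a meta-analysis that "compared the effects of Mindfulness-Based Cognitive Therapy with usual care on rumination". The stated requirement is 36 (one-tailed, 80% power), and 50 rMDD participants are declared enough for treatment effects.
- **rMDD versus ND.** The input is d = 0.686, a rumination difference between remitted patients and controls at baseline. The stated requirement is 28 per group (two-tailed), and 50 per group "should give sufficient power to draw reliable conclusions about between-group differences in changes in PC".

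The section on COVID-19 related changes reduces the physiological sample to 25 per group and adds two calculations.

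- **EEG.** The input is d = 0.59, a P3 difference between on-task and mind-wandering states: "To conduct a one sample t-test with a statistical power of 80%, a sample size of *n* = 20 participants is needed". The article says this number "is needed to draw reliable conclusions about treatment effects on PC measured with EEG".
- **Heart rate.** The input is d = 0.96, MDD patients versus healthy controls, giving 19 per group (two-tailed).

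From these two it concludes that "a sample size of *n* = 25 participants per group for (neuro)physiological measurements is sufficient to examine the effects of interventions", and for differences between rMDD and ND.

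Under Statistical analyses, aim 1 is tested by an intervention by session by time interaction and aim 2 by a group by session by intervention interaction. Under Outcome measures, HR/HRV and EEG during PC are primary for both aims.

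**The concern.** A power statement belongs to the contrast whose effect size and standard deviation went into it. Here the conclusions are about treatment effects and differences in change, while the inputs describe a mental state, a diagnosis, a baseline level, or an eight-week therapy against usual care. The size of a mind-wandering P3 effect does not tell us how far one week of mindfulness moves that effect relative to one week of fantasizing. A baseline gap in rumination does not tell us how differently two groups will change. The heart-rate input also comes from patients with MDD, whereas this trial excludes anyone with a current DSM-5 diagnosis.

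What is at stake is how the results are read. A reader who takes 25 per group as sufficient will give a null physiological interaction more weight than the design has been shown to support.

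**Working it through.** **1. Reproducing the article's figures** (exact noncentral t; alpha 0.05 is assumed, since these calculations state none)

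| Calculation | Input | Stated n | Recomputed n for 80% power |
|---|---|---|---|
| EEG, one-sample | 0.59 | 20 | 20 one-sided (power 81.5%); 25 two-sided |
| HR, two-sample, two-sided | 0.96 | 19 per group | 19 per group (82.1%) |
| Aim 1, one-sided | 0.59 | 36 | 37 per group two-sample (36 by normal approximation); 20 if paired |
| Aim 2, two-sample | 0.686 | 28 per group, two-tailed | 35 per group two-sided; 27 one-sided |

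EEG (if one-sided), HR and aim 1 (within rounding, as a two-arm number per group) reproduce. The aim 2 figure does not reproduce as two-tailed: 28 per group gives 71.3%. That is a separate slip. At 50 per group, d = 0.686 has 92.5% power two-sided, so it does not drive the present point.

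**2. Contrast used against contrast planned**

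| Input | What it measures | What it is used to claim |
|---|---|---|
| P3, 0.59 | on-task versus mind-wandering, within person | treatment effects on PC |
| HR, 0.96 | MDD versus controls, one occasion | intervention effects and group differences |
| Rumination, 0.686 | rMDD versus controls at baseline | group differences in change |
| Therapy, 0.59 | eight-week MBCT versus usual care | differential effect of two techniques, each one training session plus six 10-minute exercises |

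No row matches.

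**3. What the planned contrasts can detect**

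For each participant let D = (peri - pre) under fantasizing minus (peri - pre) under mindfulness. This session-mean contrast is a simplification, because the aim 1 model also has a time term. Let delta be the mean of D, or the group difference in that mean, divided by the SD of D.

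- Within a group of n: noncentrality = delta x sqrt(n), df = n - 1.
- Between two groups of n: noncentrality = delta x sqrt(n/2), df = 2n - 2.

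As a rough check at n = 25, (1.96 + 0.84)/sqrt(25) = 0.56 and (1.96 + 0.84) x sqrt(2/25) = 0.79. The exact t values for 80% power, two-sided 0.05, without multiplicity correction or data loss, are:

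| n per group | Within group | Between groups |
|---|---|---|
| 25 | 0.58 | 0.81 |
| 50 | 0.40 | 0.57 |

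Power at n = 25 for a range of delta:

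| delta | Within group | Between groups |
|---|---|---|
| 0.2 | 16% | 10% |
| 0.3 | 30% | 18% |
| 0.4 | 48% | 28% |
| 0.5 | 67% | 41% |
| 0.59 | 81% | 53% |
| 0.96 | over 99% | 91% |

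**4. The same limits in single-session SD units**

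D has coefficients +1, -1, -1, +1 on four sessions. With a common SD sigma and equal correlation rho, Var(D) = 4 sigma² - 4 rho sigma², so SD(D) = 2 sigma sqrt(1 - rho). The article gives no rho, so these values are assumptions:

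| rho | SD(D)/sigma | n = 25 within | n = 25 between | n = 50 within | n = 50 between |
|---|---|---|---|---|---|
| 0.5 | 1.414 | 0.83 | 1.14 | 0.57 | 0.80 |
| 0.7 | 1.095 | 0.64 | 0.89 | 0.44 | 0.62 |
| 0.8 | 0.894 | 0.52 | 0.72 | 0.36 | 0.51 |

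As an illustration for EEG, take sigma as the SD of the PC-minus-non-PC contrast. If one technique removed the whole 0.59 effect and the other left it untouched, power at n = 25 would be 52%, 73% and 89% for rho = 0.5, 0.7 and 0.8.

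**The case against.** Several points on the other side stand.

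- The EEG input is not irrelevant. The article likens it to comparing ruminative with non-ruminative trials, and the EEG procedure plans a comparison of PC with non-PC thoughts. The HR input likewise bears on a cross-sectional group difference, which is the second half of the 25-per-group claim, although its source is MDD rather than remitted MDD. Neither bears on an intervention effect.
- The authors say openly that t-tests are proxies, and two of the conclusions are introduced as suggestions. That concedes a proxy test. It does not disclose that the effect sizes belong to other contrasts.
- Repeated momentary data in mixed models may add precision. The article asserts greater sensitivity without quantifying it. Lab EEG is one visit per measurement week and ambulatory ECG one 24-hour recording.
- For non-significant LME effects, Bayes factors are planned to separate support for the null from unreliable data. This partly guards against over-reading nulls, but the article says it is unavailable for GAMs.

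A reader might go further and infer that 25 per group is too few, or that power for group differences in change is poor. The documents do not support that. They give neither an effect size for the planned contrasts nor a between-session correlation, and the answer turns on both. If the full 0.96 applied to a group difference in change under one intervention, 25 per group would have 80%, 91% and 99% power at rho = 0.3, 0.5 and 0.7. Low figures follow only if a smaller effect is assumed. Nor can a specific loss from multiplicity be computed: the correction is Benjamini–Hochberg and the family of tests is not fixed in the article.

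**Conclusion.** The point holds as a fault in what is claimed. The calculations do not support sufficiency for intervention effects or for group differences in change, at 25 per group for physiology or at 50 per group for the other measures. Sufficiency would hold at 25 per group if the standardised difference of changes reached about 0.58 within a group or 0.81 between groups, and at 50 if it reached about 0.40 or 0.57. The article offers no ground for effects that large.

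These limits assume a two-sided 0.05 test of session means, no data loss and no multiplicity correction. The conversion to single-session SDs also assumes equal variances and correlations.

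It does not follow that the trial is underpowered, or that HR/HRV and EEG must cease to be primary outcomes. Re-ranking them during data collection would be a debatable trade-off, and reporting what can be detected is enough.

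**What to change.** 1. In the Sample size section and the section on COVID-19 related changes, replace the sufficiency sentences with minimum detectable differences for the intervention by session and group by session by intervention contrasts, at n = 50 and n = 25 per group. State the assumed between-session correlations, and note that Benjamini–Hochberg correction and data loss raise these values.
2. Say what each cited effect size measures, and confine the EEG and HR inputs to the PC versus non-PC comparison and the cross-sectional group difference.
3. State that a non-significant physiological interaction is not by itself evidence of no effect. Reconcile this with the Bayes-factor step under Statistical analyses, which covers LMEs but not GAMs.

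The change is to text only: no participants are added, and no outcome or analysis is altered. The cost is a less favourable power statement.

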### Interventions

#### Mindfulness

Mindfulness-Based Cognitive Therapy is an eight-week intervention, consisting of eight training sessions of around two hours and daily practice at home of 30–40 min [24]. The intervention aims at increasing mindfulness and/or decreasing negative repetitive thoughts, and has been shown to reduce depressive relapse rates, depressive symptoms, and rumination [23, 25, 26]. In this study, we isolate two important aspects of Mindfulness-Based Cognitive Therapy, namely the professional training and short daily exercises.

In the current study, participants receive one professional training session (2 h) in the intervention in groups of 2–8 people to become familiar with the techniques, learn the basics needed for the daily exercises, and get questions answered. The training is given by a mindfulness professional and consists of psycho-education, instructions for mindfulness, and guided practice. It focuses mainly on attending to stimuli such as breathing, external sounds or bodily sensations, and becoming aware of where one’s attention is. For practical reasons, we work with two mindfulness professionals that alternate the training sessions.

After the professional training, participants receive instructions about the audio application with which they continue performing short exercises using the learned technique every day guided by an application on their smartphone customized for this research. Specifically, participants perform one short exercise (10 min) per day for in total six days. The exercises that are being performed are:day 1: attention to breathing part 1;day 2: attention to breathing part 2;day 3: attention to sounds;day 4: attention to bodily sensations;day 5: attention to thoughts;day 6: attention to emotions and feelings.

#### Positive fantasizing

The positive fantasizing technique is part of the PCT intervention [22]. PCT has been shown to be effective in preventing for depressive relapse and reducing depressive symptoms [13, 15, 16, 18, 19, 42]. In our previous study [29], we isolated a short fantasizing exercise of ten minutes from the full protocol, and found that a single session was effective at reducing negative affect when measured directly after the single-session intervention.

In the current study, we isolated the positive fantasizing technique from the PCT. In a two-hour training session by a professional trainer, participants get familiar with the positive fantasizing technique. Participants receive psycho-education about the role of dysfunctional “beliefs and schema”. The positive fantasizing technique as derived from PCT starts with identifying a dysfunctional “beliefs and schema” and subsequently fantasize about a positive “fantasy belief”. This fantasy belief can be the extreme opposite of the dysfunctional belief, but also can be a different extreme positive belief. For example, instead of “I am worthless”, participants are invited to consider the belief: “I am wonderful”. Participants are guided by the professional in choosing their limiting belief and the opposite, extremely positive belief which they investigate using the fantasizing technique. Then, participants are guided by the professional using imagery and experiencing the thoughts and feelings that would be elicited when using this, as if in an ideal world. It is made very clear that the situation they are visualizing does not have to be realistic. After using imagery techniques, participants are asked, with help of the professional, to reflect on their experience during the fantasizing exercise and to think of how they could implement this fantasy belief more in their daily life, by adapting their fantasy belief into a more practical belief, in line with how the technique is used in PCT. When participants have learned the basics of the fantasizing technique, the participants write down, together with the professional trainer, what they will be fantasizing about at home. They use the same belief every day but they can choose to apply the rule to different life situations.

Participants are asked to perform one exercise per day using the fantasizing technique (10 min), via a mobile application on their mobile phone for six days in total. Participants are guided by an audio voice leading the fantasizing exercise (e.g., asking questions such as: “Describe and imagine what it would be like if you were to live according to your fantasy belief”).

The time, instructions, and exercises are comparable for both interventions. The date and time of the exercise sessions are logged on a phone app which allows us to determine the amount of actual practice a participant engages in.

### Randomization

All participants receive both interventions, which intervention they receive first is pseudo-randomly counterbalanced across participants. Pseudo-randomization here means that individuals are randomized to either fantasizing or mindfulness as first intervention by order of inclusion. Specifically, every three weeks a new measurement session starts. Mindfulness and fantasizing alternate in three-week blocks. New sign-ups in this three-week block are allocated to mindfulness or fantasizing, in alternating order.

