The current study will combine momentary-, behavioural-, cognitive-, and physiological measures at different timescales, which could give insight into the manifestations and dynamics of PC and how it can be modified by interventions. The effects of positive fantasizing and mindfulness will be contrasted by means of affect, cognition and physiology, all sampled at high temporal density, to see whether those can clarify different mechanisms for reducing PC. Whereas positive fantasizing is potent in reducing PC by using positive phantasy to enhance positive affect and positive cognitions, mindfulness focusses on increasing awareness of the present moment and is therefore potent in reducing PC. Additionally, we will characterize sleep patterns using actigraphy and self-report. Previously, PC has been found associated with poor sleep quality and sleep onset latency, which in itself can increase PC [40]. By including individual characteristic variables (such as personality, depressive history, and childhood trauma) as potential moderators of the main effect of intervention on PC, we can gain insight in what intervention works best for whom. This could be a step towards better personalized treatment [41]. The overall aim of the current study is to study the mechanisms by which mindfulness and positive fantasizing may affect the content and dynamics of PC and thereby contribute to lower depressive relapse vulnerability. The study has three objectives.

The first objective is to study the differential mechanisms by which mindfulness and positive fantasizing affect PC in individuals vulnerable for depressive relapse. To this end, we will randomize 50 remitted MDD (rMDD) individuals in a cross-over study to both mindfulness and fantasizing, with the order of interventions randomized over participants and the same duration of the interventions. We hypothesize that both techniques change PC but that they exert these effects differently. Specifically, we expect positive fantasizing to obtain its effects by increasing positive affect and changing the content of thoughts and expect mindfulness to obtain its effects by increasing focus on the present moment.

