## Methods

### Design

To examine the differential effects of mindfulness and positive fantasizing in rMDD and ND participants, we designed an open-label intervention cross-over study in which participants received both a mindfulness- and fantasizing intervention, in randomized order. The study is conducted at the University Medical Center Groningen, the Netherlands. The study includes five phases after an initial screening that is used to determine study eligibility. Eligible participants undergo 1) an assessment of baseline characteristics using self-report questionnaires (T0); 2) pre-intervention measurement 1 including one week of baseline momentary measures using Experience Sampling Methods (ESM) ten times per day, cognitive task performance two times per day, 24-h measurements of impedance cardiography (ICG)/electrocardiogram (ECG), one-week actigraphy measurements and an EEG lab measurement and questionnaires in the lab (T1); 3) peri-intervention measurement 1 where participants practice daily with an intervention and undergo the same measurements as in pre-intervention measurement 1 (T2); 3) pre-intervention measurement 2, which takes place after a wash-out period of at least one month consisting of one-week momentary measures, two-times daily cognitive task performance, actigraphy, 24-h of ICG/ECG, and EEG measurements and questionnaires in the lab (T3); 4) peri-intervention measurement 2, including practicing with the not-yet-performed intervention and the same measurements as in pre-intervention measurement 2 (T4). An overview of the study design can be found in Fig. 1.

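### The order of interventions is assigned by systematic alternation, with no random element, but the article calls it randomized

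*Protocol article*

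**What the plan says.** The Randomization section of the protocol article labels its method pseudo-random counterbalancing and then defines it: "individuals are randomized to either fantasizing or mindfulness as first intervention by order of inclusion". The mechanics follow. Sessions are driven by the calendar, in that "every three weeks a new measurement session starts". The rule for blocks and for entrants is: "Mindfulness and fantasizing alternate in three-week blocks. New sign-ups in this three-week block are allocated to mindfulness or fantasizing, in alternating order". No list, draw or other chance element appears in the rule.

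Elsewhere the pseudo- qualifier is absent:

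- Background, first objective (remitted group): "with the order of interventions randomized over participants and the same duration of the interventions".
- Background, second objective (never-depressed group): these participants are said to be randomized in the same way.
- Design: "participants received both a mindfulness- and fantasizing intervention, in randomized order", in a study that the same sentence describes as open-label.

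Two other facts bear on the point. Mindfulness training is given "in groups of 2–8 people to become familiar with the techniques", so some grouping of entrants is built into the logistics. Recruitment also ran through the COVID-19 period: the Challenges section reports 47 participants included during the pandemic and says that it may affect mood and perseverative cognition. The section on COVID-19 changes describes a split into a laboratory phase and an online phase.

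**The concern.** Alternation by order of entry is a systematic rule. It can balance the numbers in the two orders, but it does not make the order independent of who enters and when. Once one allocation is known, so are all later ones. In an open-label study, the staff who run recruitment therefore know which intervention a given entrant will receive first, and a start date could be moved with that knowledge.

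Two things are at stake. The first is reporting: a reader of the objectives or the Design section would conclude that order was randomized for each individual, which the Randomization section does not bear out. The second is the usual justification for treating the two order groups as exchangeable. That matters if the difference between the first and second period (season, pandemic stage, online versus laboratory, familiarity with the measurements) is not the same in the two groups.

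**Working it through.** The article gives no figure that depends on the allocation method, so there is nothing to reproduce. The check is a reading of the rule against its label, followed by two short calculations.

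**1. Is there a random element?** The inputs are the four statements in the Randomization section: assignment by order of inclusion, a new session every three weeks, interventions alternating by block, and sign-ups allocated in alternating order. Each is deterministic. Given the first block or the first sign-up, the whole sequence follows. A fuller protocol could add detail, but the mechanism stated here is alternation.

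**2. Does the answer depend on how the rule is read?** The text allows two readings.

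- *By block:* everyone entering in one three-week block starts with the same intervention, and the next block starts with the other. The next allocation is known from the calendar. Order is then shared with calendar time and training group.
- *By person:* successive sign-ups within a block alternate. The next allocation is known from the previous one. The tie to calendar and training group is then much weaker.

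Foreseeability holds on both readings; the tie to calendar and training group holds only on the first.

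**3. What reaches the mindfulness-fantasizing contrast?** Work with each person's pre-to-peri change. Let θ be the true mindfulness-minus-fantasizing difference in change. Let δ₁ be the period effect on change (first minus second period) in the mindfulness-first group, and δ₂ the same in the fantasizing-first group.

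- Mean within-person difference, mindfulness first: θ + δ₁
- Mean within-person difference, fantasizing first: θ − δ₂
- Unweighted mean of the two orders: θ + (δ₁ − δ₂)/2

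A person's stable level or stable responsiveness cancels within the person. If the period effect is common (δ₁ = δ₂), it cancels too. If it is common (δ) but a share w of participants is mindfulness-first and the model has no period term, the pooled difference is wθ + wδ + (1 − w)θ − (1 − w)δ = θ + (2w − 1)δ; a period term removes this. What cannot be removed by modelling a common period effect is (δ₁ − δ₂)/2. Leaving carry-over aside, random allocation makes its expectation zero. Alternation does so only if entry is unrelated to the known order. The documents give no values for δ₁ or δ₂, so no size can be attached.

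**4. How predictable would a replacement list be?** Take a guesser who knows the block size and always picks the intervention that is behind so far.

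- Random order within known pairs: the first of each pair is guessed half the time and the second always, so (50% + 100%)/2 = 75%.
- For permuted blocks of size 2b, the expected number of correct guesses is b + (4^b / C(2b, b) − 1)/2. For b = 2: 2 + (16/6 − 1)/2 = 2.83 of 4, or 71%. For b = 3: 3 + (64/20 − 1)/2 = 4.1 of 6, or 68%. A simulation gave 71% and 68%.

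This is why block sizes should be undisclosed or varying.

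**The case against.** The rule is disclosed: the Randomization section uses the term pseudo-randomization and explains it. Everyone receives both interventions, and each has its own pre-intervention week (T1 and T3), so the planned within-subject comparison does not need the order groups to have the same baseline levels. Alternation also spreads a slow calendar trend fairly evenly over the two orders. Nothing says that applicants know the schedule, and the incentive to shift a start date is weak when both interventions will be received anyway. All of this stands, and it limits the point to labelling and a residual risk. It does not make alternation random, and the Background and Design sections omit the qualifier.

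A reader might infer more than the documents support:

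- *That order was certainly assigned to whole training groups, leaving far fewer independent allocation units than participants.* The text also admits alternation by person. Group size is given only for mindfulness, and first- and second-period attenders could train together, so a count of units cannot be derived.
- *That randomizing the order would have dealt with carry-over, or that a first-period comparison is now invalid.* Differential carry-over biases a cross-over contrast under any allocation method, and the article plans no first-period comparison.
- *That matched never-depressed controls falling into a different order is a fault of alternation.* Matching is on age, sex and education only; independent randomization would also often split pairs.

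**Conclusion.** The point holds in limited form. The article claims a randomized order, and its own rule is systematic alternation by order of inclusion. That conclusion rests on the text alone and needs no assumption. Foreseeability of the next allocation assumes only that someone involved in recruitment knows the rule and the last allocation. The link of order to calendar time and training group is conditional on the block reading.

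The within-person contrast is partly protected. The remaining exposure is selection into an order combined with a period or calendar effect that differs between the order groups, with pandemic stage and the move online as the plausible sources. Its size is unknown, and the documents do not show that selection has occurred. No stated sample size or power figure changes. This should be corrected, but it does not by itself undermine the cross-over comparison.

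**What to change.** **For allocations already made:** in the first and second objectives, the Design section and the Randomization section (heading and verb), replace the claim of randomization with allocation by alternation (quasi-randomized). State whether alternation was by three-week block or by person. Include period and order in the cross-over models; because the contrast is on pre-to-peri change, this means their interactions with session as well as their main effects. The article need not carry every model detail, so this can go in the analysis plan.

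**For participants or blocks not yet allocated:** take the first intervention from a concealed computer-generated list, held by someone who does not recruit and released only after consent and T0. If group training requires it, the list can work at block level. Block sizes should preferably be undisclosed or varying.

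**Cost:** a few words, one list and some model terms. Consecutive three-week blocks may sometimes start with the same intervention, and the design label becomes less favourable. The article expected data collection to finish in June 2024, so the new list may reach few participants or none; the wording and model changes are worth making regardless.
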